**ADDITIONAL FILE 2: STUDY PROTOCOL**

**TRIAL SUMMARY**

Bronchoscopy is a valuable diagnostic and therapeutic tool but poses a significant risk of exacerbating respiratory failure in critically ill patients. Hypoxemia and increased respiratory support requirements are common complications. High-flow nasal cannula (HFNC) oxygen therapy provides stable oxygenation and reduced respiratory distress. Traditional HFNC interfaces, however, limit bronchoscopy due to the large-bore nasal cannula occupying both nostrils. We developed a modified HFNC oxygen therapy using a single-prong cannula interface to facilitate nasal bronchoscopy. This trial aims to demonstrate whether modified HFNC oxygen therapy reduces respiratory support escalation post-bronchoscopy in patients with acute respiratory failure (ARF) compared to standard oxygen therapy (SOT).

**OBJECTIVES**

**Primary Outcome**

To determine whether modified HFNC oxygen therapy, using a single-prong cannula interface, reduces the need for escalation of respiratory support within 24 hours after bronchoscopy in patients with ARF compared with standard oxygen therapy (SOT).

Escalation was defined as meeting any of the following criteria:

1. Requirement for invasive mechanical ventilation (IMV);

2. Requirement for non-invasive ventilation (NIV);

3. Requirement for HFNC oxygen therapy;

4. An increase in support parameters without changing the level of respiratory support: For NIV patients: a >20% increase in inspiratory positive airway pressure (IPAP), expiratory positive airway pressure (EPAP), or the fraction of inspired oxygen (FiO_2_); For HFNC oxygen therapy patients: a >20% increase in flow rate or FiO_2_; For low-flow nasal cannula oxygen therapy patients: a >50% increase in oxygen flow rate.

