**Secondary Outcome**

Respiratory support escalation within 24 hours post-bronchoscopy will be further evaluated in a prespecified fixed-sequence hierarchical analysis.

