**INTERVENTIONS**

**1. Modified HFNC oxygen therapy group**

Participants in this group will receive oxygen therapy via the AIRVO 2 system (Fisher & Paykel Healthcare, New Zealand) using a single-prong nasal cannula interface. The size of the nasal cannula was selected according to the patient’s nostrils to ensure proper fit and comfort. The system will deliver heated and humidified oxygen at an initial flow rate of 60 L/min and a fraction of inspired oxygen (FiO_2_) set at 0.8, titrated as needed up to 1.0 to maintain SpO_2_ above 90% during the procedure. All participants will remain on the assigned oxygen modality during the entire bronchoscopy procedure and for post-procedural observation until clinical stabilization.

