**Step 6: Immediate post-procedure care**

Participants will continue on their allocated oxygen therapy during the recovery period. EIT measurements and arterial blood gas analysis will be performed at 2 hours after bronchoscopy. Patients will be closely monitored for respiratory deterioration or need for escalation of respiratory support.

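### The primary outcome counts needing HFNC as failure without a reference support level, so the two arms are scored on different scales

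*Protocol*

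**What the plan says.** Under Primary Outcome the objective is to show that modified HFNC "reduces the need for escalation of respiratory support within 24 hours after bronchoscopy". The composite is open: "Escalation was defined as meeting any of the following criteria". Criteria 1 and 2 are invasive and non-invasive ventilation. Criterion 3 is "Requirement for HFNC oxygen therapy". Criterion 4 covers a rise in settings at an unchanged level of support. It has a rule for NIV, one for HFNC ("For HFNC oxygen therapy patients: a >20% increase in flow rate or FiO_2") and one for low-flow nasal cannula (a rise of more than 50% in flow).

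Under Interventions, the experimental arm starts at 60 L/min with FiO2 0.8, which may go up to 1.0. Its text continues: "All participants will remain on the assigned oxygen modality during the entire bronchoscopy procedure and for post-procedural observation until clinical stabilization". The SOT arm uses a reservoir mask at 10-15 L/min until the patient is stable. Step 6 of Study Procedures repeats the point for both arms: "Participants will continue on their allocated oxygen therapy during the recovery period".

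Data Collection lists the respiratory support in use before bronchoscopy as a baseline item, but nothing makes it the comparator for escalation. Study Design states that treating clinicians cannot be blinded. Under Secondary Outcome, the same event enters again: "Respiratory support escalation within 24 hours post-bronchoscopy will be further evaluated in a prespecified fixed-sequence hierarchical analysis".

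**The concern.** HFNC is both the treatment under test and a component of the failure outcome. Allocated HFNC continues past the end of the procedure, into the 24-hour window, with no fixed end. During that time the same clinical need can be scored differently by arm: a move from mask to HFNC is an event, while remaining on HFNC is not.

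The selection criteria do not exclude patients who are already on HFNC or NIV, and criterion 4 has rules for both. Read literally, a patient on HFNC beforehand who is allocated to the mask and then resumes HFNC meets criterion 3 without having worsened.

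At stake is what the primary odds ratio means. If the arms are scored on different scales, a difference can appear when deterioration is equal, or a real difference can be masked. The term requirement has no objective threshold, and the decision to start HFNC rests with unblinded clinicians. Blinded outcome evaluation cannot undo that, because it works on events those clinicians have already generated.

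**Working it through.** The protocol gives no sample size, event rate or power (it refers these to the SAP), so there is no planned figure to reproduce. The check has three parts.

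**1. Which events are open to which arm**

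| Situation within 24 h | SOT arm | HFNC arm |
|---|---|---|
| On allocated device, now needs HFNC-level support | Event (criterion 3) | Stays on HFNC: no event under criterion 3 |
| On allocated device, settings increased | No criterion 4 rule for the mask | Event if flow or FiO2 rises by more than 20% |
| Stepped down after stabilization, later needs HFNC | Event | Event |
| On HFNC before bronchoscopy, on HFNC again afterwards | Literally an event | Not an event |
| On low flow before, still on allocated HFNC, reference = pre-bronchoscopy support | Does not arise | Could be an event by allocation alone |

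Rows 1 and 4 favour HFNC. Rows 2 and 5 count against it.

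**2. Criterion 4 thresholds from the stated settings**

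- FiO2: 0.8 × 1.2 = 0.96. Going from 0.8 to 1.0 is 1.0/0.8 − 1 = +25%, which is an event.
- Flow: 60 × 1.2 = 72 L/min must be exceeded.
- Mask: 15/10 − 1 = +50%. This would not exceed a limit of more than 50% even if the low-flow cannula rule were extended to the mask.

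Criterion 4 is thus a real route for HFNC patients, but not an equivalent one. A patient who merely goes on needing HFNC never meets it.

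**3. Illustration (all rates and sizes are assumptions)**

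Let D be the true deterioration risk, equal in both arms; f the share of it that is HFNC-level only; and q the share of those patients who are still countable in the HFNC arm.

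- SOT rate = D
- HFNC rate = D × (1 − f × (1 − q))
- Rejection probability: two-sided 5% pooled test of two proportions, 1:1, as a stand-in for the planned logistic regression.

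Example with D = 0.30, f = 0.5, q = 0 and 100 per arm:

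- HFNC rate = 0.30 × 0.5 = 0.15; OR = (0.15/0.85)/(0.30/0.70) = 0.41.
- Standard error under the null: √(2 × 0.225 × 0.775/100) = 0.0591. Under the alternative: √(0.30 × 0.70/100 + 0.15 × 0.85/100) = 0.0581.
- Φ((0.15 − 1.96 × 0.0591)/0.0581) = Φ(0.59) = 0.72. Exact binomial enumeration gives 0.73.

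| Assumption (100 per arm) | SOT | HFNC | OR | Rejection |
|---|---|---|---|---|
| D 0.30, f 0.5, q 0 | 30% | 15% | 0.41 | about 73% |
| D 0.30, f 0.5, q 0.5 | 30% | 22.5% | 0.68 | about 22% |
| D 0.20, f 0.3, q 0.5 | 20% | 17% | 0.82 | about 9% |
| Reverse: 15 points added to the HFNC arm by allocation | 30% | 45% | 1.91 | about 59%, against HFNC |
| Symmetric definition (q 1) | 30% | 30% | 1.00 | 5% |

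At 50 and 150 per arm the first row gives about 44% and 88%.

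**The case against.** The strongest reply has four parts.

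- **HFNC-arm patients are not shut out of criterion 3.** Allocated HFNC ends at stabilization while the window is 24 hours, so a patient who has stepped down can meet it later. This stands. A reader might infer that only the SOT arm can ever register an HFNC event; the text supports that only while allocated support is running.
- **There is an opposing asymmetry.** Criterion 4 has an HFNC rule ("For HFNC oxygen therapy patients: a >20% increase in flow rate" or in FiO2) and none for the mask. This stands too, and it is why the bias cannot be signed. It does not restore comparability, because two unlike routes do not make one scale.
- **Pre-bronchoscopy support may be the intended reference.** Criterion 4 speaks of an unchanged level of support, and its NIV and low-flow rules fit neither allocated device, so this reading is plausible. It would remove the problem of resumed HFNC. But it is nowhere stated, and it raises the question of HFNC-arm patients still on allocated HFNC.
- **The SAP may deal with some of this.** Sensitivity analyses are explicitly left to it, and the tier order of the win ratio may be there. So the absence of a supporting analysis is no fault here, and one cannot assert that the hierarchical outcome carries the same bias to the same degree. The definition of the primary event, however, is fixed in the protocol.

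**Conclusion.** The concern holds in limited form. Criterion 3 makes the experimental treatment a failure event with no reference level or time point, and criteria 3 and 4 together score the arms on different scales while patients are on allocated support. The primary contrast can be biased as a result, and unblinded decisions to start HFNC add to the risk.

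The net size and direction are not known. A reader might infer that the design is biased in favour of HFNC, or take 73% as the trial's false-positive rate. The documents support neither. That figure needs 30% true deterioration in both arms, half of it at HFNC level, none of it countable in the HFNC arm, and 100 patients per arm, and none of these comes from the protocol. Other equally assumed inputs give about 22% or about 9%, and the reverse reading gives about 59% against HFNC. The firm conclusion is that the result depends on an unstated choice which decides who counts as a primary event.

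**What to change.** Amend the outcome definition; allocated care need not change.

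1. Define escalation in both arms against the support level recorded before bronchoscopy, which is already collected, on one common ladder. Return to that level is not an event.
2. Count HFNC as an event in either arm when prior support was below HFNC and HFNC is used after the end of the allocated peri-procedural period. Define that end identically in both arms.
3. State how criterion 4 applies to both allocated devices, including the reservoir mask.
4. Use the same definition wherever escalation enters the hierarchical outcome.

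A supporting analysis on IMV or NIV, which neither arm allocates, is optional if the SAP does not already contain one.

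The cost is amended outcome wording and one CRF item for support level and time. The event rate may fall, in which case the SAP's planning figures would need restating.

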**2. SOT group**

Participants in the control group will receive oxygen via a standard non-rebreathing reservoir mask with a flow rate of 10-15 L/min, titrated to maintain SpO_2_ above 90% during the procedure. The mask will remain in place throughout the bronchoscopy procedure. Oxygen therapy will continue until the patient is clinically stable following bronchoscopy.

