**1. Demographics and baseline characteristics**

(1) Age, sex, body mass index (BMI);

(2) Severity scores: APACHE II, SOFA;

(3) Smoking history;

(4) Comorbidities;

(5) Indication for bronchoscopy;

(6) Respiratory support prior to bronchoscopy;

(7) Baseline vital signs;

(8) Arterial blood gas analysis.

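### The primary outcome's escalation rules do not fit the allocated devices: no rule for the control arm's reservoir mask, no reference level, and no exemption for oxygen given by allocation

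*Protocol*

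**What the plan says.** The protocol's Primary Outcome section asks whether modified HFNC "reduces the need for escalation of respiratory support within 24 hours after bronchoscopy in patients with ARF". Escalation is any of four criteria. The first two are a requirement for IMV or for NIV. The third is "Requirement for HFNC oxygen therapy", with no exception for patients randomised to HFNC. The fourth is "An increase in support parameters without changing the level of respiratory support", with thresholds by device: above 20% in IPAP, EPAP or FiO2 on NIV; "For HFNC oxygen therapy patients: a >20% increase in flow rate or FiO_2" for HFNC; and "For low-flow nasal cannula oxygen therapy patients: a >50% increase in oxygen flow rate". The section does not say what the increase is measured from.

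Under Interventions, the HFNC arm starts at 60 L/min with FiO2 "set at 0.8, titrated as needed up to 1.0 to maintain SpO_2_ above 90% during the procedure". The SOT arm receives "a standard non-rebreathing reservoir mask with a flow rate of 10-15 L/min, titrated to maintain SpO_2_ above 90" percent, also during the procedure. Both Interventions sections and Step 6 of the Study Procedures keep the allocated oxygen running after bronchoscopy, until the patient is stable.

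Data Collection lists "Respiratory support prior to bronchoscopy" among the baseline items but does not tie it to the outcome.

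**The concern.** Two things are absent from a definition that the protocol otherwise writes out device by device: a rule for the device assigned to the control arm, and the level from which an increase is counted. A third gap makes them matter. The 24-hour window opens while patients are still on the oxygen they were randomised to, and nothing says whether that oxygen, or its settings, can itself count as escalation.

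Whether a patient has a primary event may then depend on the device assigned and on a scoring choice made later, rather than on whether the patient worsened. Two assessors could apply the written text to the same records and reach different event counts, with the difference falling unequally on the arms. The key secondary outcome is a hierarchical analysis of the same escalation, so it is exposed to the same ambiguity.

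**Working it through.** The protocol states no event rate or sample size, so there is no planned figure to reproduce. The check applies the written thresholds to the protocol's own settings under each reference level that a reader could choose.

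**Inputs**
- HFNC arm: 60 L/min initially; FiO2 0.8, up to 1.0 (Interventions, section 1).
- SOT arm: reservoir mask, 10 to 15 L/min (Interventions, section 2).
- Thresholds: above 20% for HFNC flow or FiO2; above 50% for nasal cannula flow (Primary Outcome, criterion 4).
- Formula: change in % = 100 × (new / reference − 1).

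**Reference 1: support before bronchoscopy**
- Previously on HFNC, allocated to HFNC. The assigned flow exceeds +20% if the prior flow was below 60 / 1.2 = 50 L/min (for example, 40 to 60 is +50%; 50 to 60 is exactly +20% and does not count). The assigned FiO2 exceeds +20% if the prior value was below 0.8 / 1.2 = 0.67 (for example, 0.5 to 0.8 is +60%).
- Previously on low-flow oxygen, allocated to HFNC. Continuing HFNC after the procedure can be read as meeting criterion 3.
- Previously on nasal cannula, allocated to the mask. No written rule applies. If the cannula rule were borrowed, a prior flow below 10 / 1.5 = 6.67 L/min would trigger at 10 L/min, and a prior flow below 15 / 1.5 = 10 L/min would trigger at 15 L/min.

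**Reference 2: the assigned starting setting**
- HFNC arm, FiO2 0.8 to 1.0: 100 × (1.0 / 0.8 − 1) = +25%, above the limit.
- HFNC arm, flow: would have to exceed 60 × 1.2 = 72 L/min.
- SOT arm: no rule for the mask. With the cannula rule borrowed, 10 to 15 L/min is 100 × (15 / 10 − 1) = +50% exactly, so the full stated range does not exceed the limit.

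**Reference 3: the setting at the end of the procedure**
- HFNC arm: a patient above FiO2 1 / 1.2 = 0.83 cannot rise by more than 20%.
- SOT arm: still no rule for the mask.

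**Timing.** The titration ranges are stated for the procedure itself, and the outcome window follows it. A titrated setting can therefore bear on the outcome only if it is carried into the recovery period. The protocol continues the allocated modality there but gives no settings for that period.

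**Other routes for the SOT arm.** A control patient who worsens can be counted through criteria 1, 2 or 3, including a move from mask to HFNC, or through criterion 4 once on a listed device. This works against the pattern above.

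**The case against.** The strongest reply is that criterion 4 was never meant to grade the allocated devices. It lists NIV and low-flow cannula, to which nobody is randomised, so the list fits the patient's own support before bronchoscopy. The wording about an unchanged level of support points the same way. On that view the mask is a procedural device, its absence from the list is expected, and a device given by randomisation is not a requirement arising after bronchoscopy. The titration ranges also belong to the procedure, which precedes the window.

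Much of this stands. Pre-bronchoscopy support is the most natural reference, and a sensible assessor would probably not count allocation alone. But neither point is written down, and choosing that reference does not settle how to score the hours when allocated oxygen is still running: HFNC has a rule in that period and the mask has none. Nor is this only detail left for a SAP. The Statistical Analysis section defers sample size, sensitivity analyses and missing data, whereas the outcome and its thresholds are set out in the protocol itself.

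Three stronger readings are tempting and are not supported:
- A reader might infer that a control patient can never have a primary event. That holds only for criterion 4, and only while the patient is on the mask; criteria 1 to 3 remain open.
- A reader might infer that the definition is biased against HFNC. The move from mask to HFNC under criterion 3 can add events in the SOT arm, so the net direction is open.
- A reader might assume that, say, 5 to 10% of HFNC patients have FiO2 raised afterwards and read this as 5 to 10 percentage points of spurious events. The document gives no such rate. Some of those patients may have truly worsened or have another qualifying event, and similar worsening in the SOT arm can count through criteria 1 to 3.

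**Conclusion.** The concern holds as a defect in the definition of the primary outcome. Criterion 4 omits the control arm's device, no reference level is named, and criteria 3 and 4 are silent on oxygen given by allocation, although that oxygen runs into the outcome window in both arms. As written, continued or increased HFNC can meet a criterion while continued or increased mask oxygen meets none under criterion 4, so scoring depends on arm.

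The thresholds in the check are exact arithmetic on the protocol's settings. How many patients they affect depends on the mix of prior support and on the settings used in recovery, neither of which the document gives. No size or direction of bias can therefore be stated. The conclusion rests on a literal reading of the text and on allocated oxygen still being in use after the procedure, as the protocol says it is.

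**What to change.** In the outcome definition:
1. Name the support and settings recorded before bronchoscopy as the single reference for criterion 4.
2. State that the allocated device and its protocol-set settings do not by themselves count under criterion 3 or 4.
3. State how time on the reservoir mask is scored, so that remaining on, or increasing, allocated oxygen is judged by the same rule and at the same clock times in both arms.
4. Reconcile the Primary Outcome section with both Interventions sections and with Step 6 of the Study Procedures.

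The cost is outcome wording and possibly some case report form fields. Data Collection lists prior support without its settings and does not explicitly list flow or FiO2 after the procedure, so these may need to be added. No extra patients are needed, and treatment in either arm need not change. Replacing all thresholds with a device-neutral FiO2 endpoint and a conversion table is not required: it would redefine the outcome and is a debatable trade-off.

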**Secondary Outcome**

Respiratory support escalation within 24 hours post-bronchoscopy will be further evaluated in a prespecified fixed-sequence hierarchical analysis.

**Other outcomes**

1. To evaluate whether modified HFNC oxygen therapy reduces the rate of endotracheal intubation at 24 hours, 7 days, and 28 days after bronchoscopy.

2. To assess whether modified HFNC oxygen therapy improves oxygenation stability, as measured by peripheral oxygen saturation (SpO_2_) levels during bronchoscopy.

3. To determine whether the use of modified HFNC oxygen therapy is associated with a reduced incidence of procedural interruptions during bronchoscopy.

4. To assess whether modified HFNC oxygen therapy shortens the procedure duration compared with SOT.

5. To assess the impact of modified HFNC oxygen therapy on ICU and hospital length of stay.

6. To evaluate whether modified HFNC oxygen therapy reduces all-cause mortality at 28 days, 60 days, and 90 days.

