**Step 5: Bronchoscopy procedure**

Bronchoscopy will be performed via nasal access following standard clinical practice. Diagnostic interventions such as bronchoalveolar lavage (BAL), bronchial brushing, endobronchial biopsy, or transbronchial lung biopsy will be performed when clinically indicated. Any procedural interruption or adverse events will be documented in real time. Vital signs and EIT parameters will be recorded at five predefined time points: T0, before bronchoscopy; T1, upon insertion of the bronchoscope into the nasal cavity; T2, at the end of the procedure; T3, 10 minutes after bronchoscopy; and T4, 2 hours after bronchoscopy.

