**2. Procedural data**

(1) Type of bronchoscopy and diagnostic interventions: BAL, bronchial brushing, endobronchial biopsy, transbronchial lung biopsy;

(2) Volume of BAL fluid instilled and recovered;

(3) Duration of bronchoscopy;

(4) Vital signs, including respiratory rate, heart rate, mean arterial pressure, and SpO_2_, as well as EIT measurements such as tidal impedance variation (TIV) and changes in end-expiratory lung impedance (ΔEELI), will be recorded at five predefined time points: T0, T1, T2, T3, and T4;

(5) Arterial blood gas analysis at T4.

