**3. Intra-bronchoscopy and post-bronchoscopy events**

(1) Events during bronchoscopy: agitation, bronchospasm, arrhythmias/tachycardia ≥150 bpm, hypertension, epistaxis, mucosal bleeding;

(2) Events within 24 hours post-bronchoscopy: transient fever, pneumothorax, hemorrhage;

(3) Lowest SpO_2_ recorded during bronchoscopy;

(4) Number of procedure interruptions.

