**STATISTICAL ANALYSIS**

All statistical analyses will be performed according to the predefined Statistical Analysis Plan (SAP). Analyses will follow the intention-to-treat principle, with additional per-protocol analyses conducted as appropriate.

Descriptive statistics will be used to summarize baseline characteristics. Categorical variables will be compared using the chi-square test or Fisher’s exact test, and continuous variables will be analyzed using t-tests or Mann–Whitney U tests, as appropriate.

The primary outcome (escalation of respiratory support within 24 hours) will be analyzed using logistic regression The key secondary outcome (respiratory support escalation assessed hierarchically) will be analyzed using the win ratio method in a prespecified fixed-sequence hierarchical framework to prioritize endpoints and control for multiplicity. Time-to-event outcomes will be analyzed using Kaplan–Meier survival curves and log-rank tests.

All statistical tests will be two-sided, and a p-value <0.05 will be considered statistically significant.

Details of sample size calculation, sensitivity analyses, and handling of missing data are provided in the SAP.

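### Procedure duration is collected without completion status, so a bronchoscopy abandoned early counts as a favourably short one (minor)

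*Protocol*

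**What the plan says.** Under Other outcomes, the protocol gives duration a direction of benefit: "To assess whether modified HFNC oxygen therapy shortens the procedure duration compared with SOT". The preceding item asks whether modified HFNC is "associated with a reduced incidence of procedural interruptions during bronchoscopy".

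The Data Collection section lists "Duration of bronchoscopy" under Procedural data and "Number of procedure interruptions" under Intra-bronchoscopy and post-bronchoscopy events. Step 5 of Study Procedures adds that "Any procedural interruption or adverse events will be documented in real time", and it fixes one closing time point, "T2, at the end of the procedure". That label is the same whether the procedure was finished or given up.

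No section mentions an incomplete or abandoned bronchoscopy, and neither data list has a completion-status item. For a measure such as duration, the Statistical Analysis section offers only the general rule that "continuous variables will be analyzed using t-tests or Mann–Whitney U tests, as appropriate".

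**The concern.** Time in the procedure is a clean measure of efficiency only if everyone gets through the planned procedure. A patient who desaturates and has the scope withdrawn after a few minutes has an observed duration, and it is a short one. Because shorter is read as better, the failed procedure ranks ahead of a fully tolerated one.

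If abandonment is equally common in both arms, this mainly adds noise. If it is more common in one arm, it shifts the comparison towards that arm, and enlarging the trial does not remove the shift. An intervention that helps patients complete the procedure could then appear to prolong it.

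The gap is one of measurement. A scoring rule can be left to the SAP, but no SAP can use a completion status that was never recorded. Nor is an abandoned procedure a missing value that missing-data rules would pick up, because it has a recorded time.

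**Working it through.** **Inputs.** The protocol states no duration, SD, interruption rate or abandonment rate, so there is no figure of its own to reproduce. Every number below is an assumption chosen to show direction and rough size.

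**1. Mean duration, no true difference.** Assume 15 min for a completed procedure in both arms, 5 min for an abandoned one, and 2% abandonment on HFNC. With abandonment rate a:

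arm mean = (1 − a) × 15 + a × 5

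HFNC: 0.98 × 15 + 0.02 × 5 = 14.8 min.

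| SOT abandonment | SOT mean (min) | HFNC − SOT (min) |
|---|---|---|
| 5% | 14.5 | +0.3 |
| 10% | 14.0 | +0.8 |
| 20% | 13.0 | +1.8 |

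HFNC looks slower although completed procedures take the same time.

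**2. Mean duration, true 1-min benefit on completed procedures.** HFNC mean = (1 − a) × 14 + a × 5.

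| Abandonment SOT / HFNC | SOT mean | HFNC mean | HFNC − SOT |
|---|---|---|---|
| 2% / 1% | 14.8 | 13.91 | −0.89 |
| 5% / 2% | 14.5 | 13.82 | −0.68 |
| 10% / 3% | 14.0 | 13.73 | −0.27 |
| 20% / 5% | 13.0 | 13.55 | +0.55 |

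The benefit is diluted in all four cases and changes sign only in the last.

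**3. SOT abandonment that cancels a real benefit.** Setting the arm means equal gives a(SOT) = (15 − HFNC mean) / 10. With HFNC abandonment between 1% and 5%:

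- 0.5-min benefit: about 6% to 10%
- 1-min benefit: about 11% to 15%
- 2-min benefit: about 21% to 24%

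**4. The rank test alone does not help.** Suppose completed times have the same distribution in both arms and every abandoned time is shorter than every completed one. For a random pair, one patient per arm, the probability that SOT is shorter minus the probability that HFNC is shorter is

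a(SOT) × (1 − a(HFNC)) − a(HFNC) × (1 − a(SOT)) = a(SOT) − a(HFNC).

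With 2% on HFNC and 5%, 10% or 20% on SOT, this is 3, 8 or 18 percentage points in favour of SOT. Ranking abandoned procedures last gives the same size in the opposite direction.

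**5. Interruptions, for comparison.** Assume 20% (SOT) and 10% (HFNC) of completed procedures have at least one interruption. Arm proportion = (1 − a) × p + a × c, with c = 1 if abandonment counts as an interruption and c = 0 if it does not and no interruption came before it.

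| Abandonment SOT / HFNC | Difference, counted | Difference, not counted |
|---|---|---|
| 5% / 2% | −12.2 points | −9.2 points |
| 10% / 3% | −15.3 points | −8.3 points |
| 20% / 5% | −21.5 points | −6.5 points |

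Counted, the difference moves in the right direction. Not counted, it shrinks but keeps its sign. With HFNC abandonment of 2% to 5%, reversal would need about 51% to 53% abandonment on SOT, or about 12% to 15% if the underlying proportions were nearly equal (20% and 18%).

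**The case against.** **The scoring rule may be in the SAP.** It may, and its absence from the protocol alone would be no finding. What stands is that the protocol itself lists the data to be collected, and completion status is not among them. The full CRF is not shown and may contain such an item. If so, only the scoring sentence is needed.

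**Other items partly reveal completion.** The interventions performed, lavage volumes, lowest saturation and number of interruptions are all recorded. They help, but lavage is done only where indicated and no planned volume is listed, so completion cannot be read off reliably.

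**The size is assumed, and one opposing effect is left out.** Both are true. Pauses for desaturation would lengthen completed SOT procedures, which works against the truncation. The second calculation allows for this through a true HFNC benefit, and the sign then survives in three of four scenarios.

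**Ranking abandonments last is a choice.** It turns duration into a composite, and applied to every abandonment it would also penalise stops unrelated to oxygenation, such as bleeding. That is why the fix limits it to respiratory intolerance or to a sensitivity analysis.

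**Stronger readings to avoid.** A reader might infer that the interruption objective can be misled in the same way. The documents do not support this: that objective is worded as an incidence, a stop for hypoxaemia would naturally be logged as an interruption, and it then counts in the right direction. What remains is that the term is undefined and that the objective names an incidence while the data list names a count. A reader might also infer that the trial expects more abandoned procedures under SOT. The Trial Summary says only that hypoxaemia is a common complication. No section gives an expected rate of abandonment or a difference between arms.

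**Conclusion.** The point holds for duration, as a minor one. The protocol reads shorter as better and lists nothing that separates a quick procedure from an abandoned one, so unequal abandonment biases the comparison in favour of the arm with more of it. The direction follows from the protocol's text. The size does not: under the assumed values it is 0.3 to 1.8 min with no true difference, and a real benefit is more likely to be diluted than reversed unless abandonment is high or the benefit is small.

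For interruptions, only a clarification is warranted. Both are Other outcomes, and neither the primary outcome nor the win-ratio analysis uses them.

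**What to change.** 1. **Data Collection, Procedural data or the events list:** add one item recording whether the planned bronchoscopy was completed or abandoned, with the reason, entered at the time of the procedure.
2. **Duration:** report the proportion completed by arm next to duration. Compare duration with the Mann–Whitney test that the Statistical Analysis section already allows, ranking procedures abandoned for respiratory intolerance worst, either as the main comparison or as a sensitivity analysis. State how procedures abandoned for other reasons are ranked. Operators know the allocation when they give the reason, so the proportion completed should cover abandonment for any reason.
3. **Interruptions:** state that an abandonment counts as an interruption, and analyse the proportion with at least one, as the objective is worded, rather than the raw count.

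The cost is one CRF field and two or three sentences. The downside is that the duration result becomes a rank comparison rather than a difference in minutes, and it mixes speed with completion, so the proportion completed must be read beside it. The change concerns recording and scoring only, not when a procedure should be stopped. It is best made before procedures are done, because completion status may be hard to recover afterwards.
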